### NIRS acquisition

Functional near-infrared spectroscopy (fNIRS) is conducted with the ETG-4000 Optical Topography System (Hitachi Medical Co., Tokyo, Japan), a continuous wave system working with two different wavelengths (695 ± 20 and 830 ± 20 nm) and a temporal resolution of 10 Hz. Relative changes of absorbed near-infrared light are transformed into concentration changes of O_2_Hb and HHb by means of a modified Beer-Lambert law. Two optode sets (each consisting of eight emitters and seven detectors; interoptode distance: 30 mm) are placed over left and right prefrontal regions (6 x 12 cm each). They are orientated according to the standard EEG positions F3, T3 and F4, and T4 [72,73].

### Working memory task (n-back task)

A letter *n*-back task (see, for example, [36]) with three different conditions is used to investigate functions of working memory (WM). In the 0-back condition (marginal WM load), participants have to press a response button whenever a previously defined target letter appears in a stream of different letters. In the 1-back condition (low WM load), participants have to press the response button whenever the letter appearing on the computer screen is identical to the preceding letter. In the 2-back condition (high WM load), participants have to press the response button whenever the current letter is identical to the letter presented two trials before. These three conditions are performed alternately in a blockwise fashion, separated by 30-s resting segments during which participants are instructed to sit still and relax. Letters are presented in pseudo-randomized order with a presentation time of 300 ms and an interstimulus-interval of 1700 ms, resulting in 30-s task segments. Each of the three task conditions is conducted three times; that is, participants perform nine task segments. Additionally, a 10-s baseline period precedes the first task segment. For all three conditions, a total of 12 target trials appear across task segments. The button presses are recorded, and the number of errors and correct responses, as well as the RT, will be analyzed as behavioral data. The task lasts for about 10 min.

### Response inhibition task (Go-NoGo task)

A Go-NoGo task is used to investigate executive functions in terms of response inhibition processes (see [74]). The task is designed in a block-wise fashion, comprising four Go and four NoGo blocks with a duration of 30 s each. These two blocks are presented in an ABABABAB design. In each block, a stream of 16 letters is presented (stimulus presentation time: 175 ms; interstimulus interval: 1700 ms). Participants are instructed to respond with their dominant hand via button press to each letter, but to withhold their response when the letter ‘N’ is presented. While in the Go blocks no ‘Ns’ are shown, 50% of the letters in the NoGo blocks are ‘Ns’. RTs and errors are recorded, whereupon the latter are classified into commission errors (false alarms) and omission errors (missing reactions). The task lasts for about 8 min.

### Verbal fluency task

A verbal fluency task is used to investigate executive functions. In the phonological condition (letters), participants have to name as many nouns as possible that come to their mind with a previously defined first letter for 30 s. In the semantic condition (category), participants have to name as many nouns as possible that come to their mind out of a previously defined category for 30 s. In the control condition (weekdays), participants have to name the weekdays for 30 s. These three conditions are performed alternately in a blockwise fashion, separated by 30-s resting segments during which participants are instructed to sit still and relax. Each of the three task conditions is conducted three times; that is, participants perform nine task segments. Additionally, a 10-s baseline period precedes the first task segment. The task lasts for about 10 min.

### Primary and secondary endpoints

As a primary outcome, the changes in core symptoms will be assessed by the ADHS-SB (self-report) and the FEA-AFB as well as WRI (third party evaluation). Variables of secondary outcome will include cognitive factors (that is, attention, intelligence, response inhibition, and working memory) and changes in specific EEG/ERP and NIRS parameters (that is, relative and absolute power and frequency ratios, concentration changes in O_2_Hb and HHb), as well as achievement of self-regulation.

For the pre- and postevaluation, the independent variable is the treatment (SCP, NIRS, or placebo feedback). In addition, for the comparison of the neurophysiological and cognitive data the health status (healthy and ADHD participants) constitutes another independent variable.

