## Methods/Design

In this proof-of-principle study, a total of 60 adult participants diagnosed with ADHD (combined, hyperactive, or inattentive type) are randomly blockwise assigned to SCP, NIRS, or electromyogram (EMG) feedback groups (n = 20 each) stratified for age, sex, and educational level. This is the first study to investigate and compare the efficacy of these treatment modalities in an adult ADHD population.

Twenty healthy controls matched for age, sex, IQ, and pre- and post-treatment duration will be included in the neurophysiological assessments for pre- and post-treatment measurement in order to establish “expected” activation patterns and allow for a more thorough interpretation of changes following the neurofeedback treatment. The study objectives are as follows:Assess whether there are physiological differences (EEG and ERP) in ADHD participants compared to healthy controls.Assess whether adult participants are able to demonstrate learning of cortical self-regulation.Assess whether treatment leads to an improvement in cognition (that is, attention and working memory) and behavior (that is, restlessness and impulsivity), and changes in specific EEG or NIRS parameters.Assess whether specific methods and protocols are more efficacious in changing behavioral, cognitive, and EEG and NIRS outcome variables.Assess whether changes are stable at the 6-month follow-up.Assess whether specific methods and protocols differ in the stability of cortical self-regulation and clinical effects at the 6-month follow-up.Assess whether the efficiency of the different training protocols differs depending on individual neurocognitive baseline parameters (for example, frontal lobe activation during neuropsychological assessments; baseline CNV etc.).

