### Statistics

#### Sample-size calculation

The basic problem with determining the number of cases needed is that there are no comparable studies about SCP training in adults and even fewer studies about the influence of the blood flow regulation. For this study, the planned sample size is based on a power calculation of a meta-analysis by Arns *et al*. [75] that showed a grand mean effect size of 0.81 for improvements in inattention in children with ADHD by EEG neurofeedback training as compared to passive or semi-active (for example, EMG) placebo trainings. Assuming a pre-defined α of 0.05, a power criterion of at least 80%, and one-sided testing, such an effect size would indicate a required sample size of n = 20 per treatment group.

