### Statistical analysis

#### Electroencephalogram, near-infrared spectroscopy, electromyogram and behavioral data

All dependent variables will be tested for effects within and between groups by an analysis of variance (ANOVA) (three groups x four assessment points). For the comparison of pretest-data between ADHD and healthy subjects, t-tests and/or one-way ANOVAs will be applied. If normal distribution cannot be assumed, non-parametric tests will be used.

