## Discussion

This paper presents the protocol and design of a randomized controlled trial with two types of neurofeedback (SCP and NIRS) and an active control (EMG biofeedback) condition for adults with ADHD. This is the first study to systematically investigate neurofeedback in adults with ADHD. It is also the first study to compare SCP and NIRS feedback to an active control condition on the one hand and to investigate this in an adult ADHD population on the other hand.

If one or both feedback types are superior to the control condition, a first step will be made towards a new acknowledged treatment option for adult ADHD.

This is not the “gold standard” design for treatment studies, which is a placebo-controlled randomized double blind design [76]. The problems with this approach are widely discussed elsewhere [77,78]. Therefore, to allow for all therapeutic aspects of neurofeedback therapy to come into effect, such as a good patient-therapist relationship, psychoeducation, and strengthening of self-efficacy expectations, we decided to use an active control condition that was used in other studies before. The study design was based on a study protocol of a multicenter treatment study with ADHD children [57]. The use of EMG feedback as an active control condition is based on the rationale that EMG feedback is not an “empty” treatment, but will induce identical nonspecific (placebo) effects that will help to differentiate between specific effects of the neurofeedback and nonspecific effects from the above-mentioned aspects.

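### Three unranked primary instruments, no declared primary visit and an either-arm success statement leave the deciding test open, while the sample size covers only one unadjusted comparison

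*Protocol article*

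**What the plan says.** Under Primary and secondary endpoints, the protocol article states: "As a primary outcome, the changes in core symptoms will be assessed by the ADHS-SB (self-report) and the FEA-AFB as well as WRI". The three instruments are a self-rating, an informant rating and an interview. That section also mentions a pre/post evaluation with treatment as the independent variable, but it does not call any visit primary. Under Study flow, assessments are repeated at mid-treatment, post-treatment and 6 months.

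Under Statistical analysis: "All dependent variables will be tested for effects within and between groups by an analysis of variance (ANOVA) (three groups x four assessment points"). No pairwise contrasts are named there.

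Under Sample-size calculation, the effect comes from a meta-analysis that "showed a grand mean effect size of 0.81 for improvements in inattention in children with ADHD by EEG neurofeedback training". The design settings follow: "Assuming a pre-defined α of 0.05, a power criterion of at least 80%, and one-sided testing". The result: "such an effect size would indicate a required sample size of n = 20 per treatment group".

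The Discussion says what a positive result would mean: "If one or both feedback types are superior to the control condition, a first step will be made towards a new acknowledged treatment option".

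Table 1 lists the ADHS-SB (under the label ADHD-SB) and the FEA-AFB at screening, in-between test, post-test and follow-up. It lists the WRI at screening, post-test and follow-up only.

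**The concern.** Which instrument and which visit decide the trial is a protocol matter, not detail that can be left to an analysis plan. The endpoint section addresses it and leaves it open. Three instruments share the primary label, two active arms are set against one EMG arm, and the visit could be the post-test, the 6-month follow-up or all assessment points together.

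Two things are at stake. First, the chance of a false-positive primary result is not fixed at 0.05, because several tests could carry the conclusion. Second, the instruments may disagree. Under Randomization and blinding, neither participants nor assessors are blinded, so self, informant and interviewer ratings could plausibly diverge. With no rule stated in advance, the deciding instrument could be picked once results are known.

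**Working it through.** **1. The plan's own figure.** Inputs from Sample-size calculation: d = 0.81, one-sided α = 0.05, power 80%.

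- Normal approximation: n = 2(1.645 + 0.842)²/0.81² = 18.8, so 19 per group.
- Exact noncentral t: n = 20. With noncentrality 0.81·√(20/2) = 2.56, 38 df and critical value 1.686, power is 80.8%.
- Two-sided versions give 24 (normal) or 25 (t) and do not reproduce it.

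So 20 per group is the size for one outcome, one contrast and no adjustment.

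**2. Chance of at least one false-positive primary result.** Setting: three arms of 20, a shared EMG arm, three instruments with common correlation ρ, one visit, and no true effects. Omnibus tests are one-way three-group F tests on change; contrasts are pairwise t-tests at 0.05. The documents give no ρ, so it is an assumption. Reference values under full independence are 1 − 0.95³ = 14.3% for three tests and 1 − 0.95⁶ = 26.5% for six. Simulation with 40,000 runs per setting:

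| Reading | ρ = 0.3 | ρ = 0.5 | ρ = 0.7 |
|---|---|---|---|
| Any of three omnibus F tests | 13.8% | 12.6% | 11.5% |
| Any of six one-sided contrasts, no gate | 21.8% | 19.8% | 17.8% |
| One-sided contrast, only after that instrument's significant F | 6.4% | 5.8% | 5.6% |
| Two-sided contrast, only after that instrument's significant F | 11.3% | 10.5% | 9.4% |

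Repeat simulations agree within about one percentage point. For ρ from 0 to 0.9, the ungated six-contrast figure runs from 24% down to 14% one-sided and from 25% to 15% two-sided. The gated figure runs from 7% to 4% one-sided and from 12% to 7% two-sided.

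**3. More than one visit.** Following Table 1, two instruments have three post-baseline visits and the WRI has two. That is 3 + 3 + 2 = 8 tests per contrast, or 16 in all. With assumed between-instrument correlation 0.3-0.7 and between-visit correlation 0.5-0.7, the ungated one-sided figure is 30-42%.

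**4. What error control costs at 20 per arm** (d = 0.81, noncentrality 2.56):

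- One-sided Dunnett, two contrasts, 57 df: critical value about 1.96, power per contrast 73%.
- Bonferroni over two contrasts (one-sided 0.025): power 70%; 25 per arm needed by the t calculation.
- Bonferroni over all six tests (one-sided 0.0083): power 53%.
- Fixed order of the two contrasts: the first keeps 0.05 and about 81%.
- Dunnett with baseline adjustment: noncentrality becomes 2.56/√(1 − r²). At an assumed baseline-post correlation r = 0.5 it is 2.96, and power is about 84%. At r = 0.3 it is about 77%.

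**5. Table 1 against the ANOVA.** The stated analysis needs four assessment points for every dependent variable. The WRI, one of the three primary instruments, has three in Table 1, so it cannot enter that model as written.

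**The case against.** A reader might infer that three instruments and two contrasts are each tested at 0.05, and that a false claim of benefit therefore has about a 20% chance. The document does not support that as a statement of fact. The only analysis it describes is an omnibus ANOVA per variable, and both 0.05 and one-sided testing appear only in the sample-size paragraph. Six ungated contrasts are a construction from the endpoint, sample-size and Discussion sections together. Gating contrasts on the omnibus test is a natural way to use an ANOVA, and it brings the one-sided figure close to nominal. The endpoint sentence does not say that any one instrument suffices, nor that all must succeed.

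It is also fair that the Discussion sentence speaks only of a first step and is not a formal success criterion. The study is labelled proof-of-principle, and the mechanics of multiplicity control may sit in an analysis plan that is not shown.

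These points stand and limit the size and severity of the finding. They do not remove it. No gate is stated either, and a three-group F test cannot deliver the one-sided test that the sample size assumes. Even the analysis as written gives 11-14% if any of the three primary omnibus tests counts. An unseen Bonferroni or Dunnett adjustment would miss the stated 80% power at 20 per arm without some further gain. A fixed order would keep it for the first test, but requires naming what comes first, which is what the protocol leaves open.

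**Conclusion.** The point holds as an ambiguity in the primary objective, and it should be fixed. The primary outcome is three unranked instruments, no visit is declared primary, either active arm may carry the conclusion, and the sample size allows for none of this.

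No single error rate can be attached to the plan. At one visit and with assumed between-instrument correlations of 0.3 to 0.7, the range runs from about 5-7% (one-sided contrasts gated on the omnibus test), through 11-14% (any omnibus test), to 17-22% (six ungated one-sided contrasts). Gated two-sided contrasts give 7-12% over correlations from 0 to 0.9. Letting several visits count raises the figure, by an amount that depends on a between-visit correlation the documents do not give. The proof-of-principle label lowers the severity, but it does not settle which result counts as success.

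**What to change.** - Name one primary instrument and one primary visit, for example the post-test. The choice of instrument is the sponsor's and should weigh the lack of blinding of participants and assessors. Availability does not separate the ADHS-SB from the FEA-AFB, since Table 1 lists both at the same four points.
- Test SCP against EMG and NIRS against EMG with a one-sided Dunnett procedure at overall 0.05.
- Make the other two instruments and the 6-month results secondary outcomes, tested in a stated order.
- Reconcile the absence of the WRI at the in-between test in Table 1 with the four-point ANOVA.
- Restate the power.

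**Cost.** No new data are needed, but this is more than a wording change. Dunnett at 20 per arm lowers power per contrast from about 81% to about 73%, below the 80% criterion. The sponsor can accept and state that, fix the order of the two contrasts (about 81% for the first), or adjust for baseline (about 84% if the baseline-post correlation is 0.5, about 77% if it is 0.3).

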### Risks and side effects

The medical risks of EEG and EMG recordings are few, rare, and quickly remediable. For individuals who have highly sensitive skin, there is the possibility of temporary skin irritation caused by cleaning the scalp with abrasive cleaning gel and the subsequent application of electrode gel to improve the electrical conductivity between the skin and electrode. No electrical current is applied; only electrical output is recorded from the sensors. Additionally, the EEG acquisition and neurofeedback equipment used in this investigation are certified as medical devices (class IIa. EU) for the use with human subjects.

Risks associated with EEG- or EMG-feedback treatment are also few, rare, and quickly remediable. For individuals who are highly sensitive or susceptible, neurofeedback may precipitate a headache (muscle tension induced), hot flash, or mild anxiety (performance induced). Potential problems can be minimized and averted by obtaining an appropriate medical history prior to treatment. Side effects are typically mild, transient, and quickly remediable, allowing participants to continue the treatment.

NIRS is an optical method for examining the oxygen level of cortical tissue. Light from the near-infrared spectrum (700–1000 nm wave length) can penetrate the skull of an adult head and can be absorbed by two chromophores (oxygenated hemoglobin or reduced hemoglobin). As the two types of hemoglobin differ in the amount of light they absorb, concentration changes of both types of hemoglobin in the brain tissue can be derived, and from this, information about the brain activity can be drawn [31]. An advantage of this method, especially for ADHD participants, is its relative insensitivity to movement artifacts. There are no medical risks associated with NIRS recording; whereas for the neurofeedback aspect, side-effects are expected to be similar to the ones observed for EEG neurofeedback protocols (see above). All measurements will be conducted in the presence of an experienced research assistant.

### Statistics

#### Sample-size calculation

The basic problem with determining the number of cases needed is that there are no comparable studies about SCP training in adults and even fewer studies about the influence of the blood flow regulation. For this study, the planned sample size is based on a power calculation of a meta-analysis by Arns *et al*. [75] that showed a grand mean effect size of 0.81 for improvements in inattention in children with ADHD by EEG neurofeedback training as compared to passive or semi-active (for example, EMG) placebo trainings. Assuming a pre-defined α of 0.05, a power criterion of at least 80%, and one-sided testing, such an effect size would indicate a required sample size of n = 20 per treatment group.

### Statistical analysis

#### Electroencephalogram, near-infrared spectroscopy, electromyogram and behavioral data

All dependent variables will be tested for effects within and between groups by an analysis of variance (ANOVA) (three groups x four assessment points). For the comparison of pretest-data between ADHD and healthy subjects, t-tests and/or one-way ANOVAs will be applied. If normal distribution cannot be assumed, non-parametric tests will be used.

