### Inclusion and exclusion criteria

Participants include adults 18 years and older who meet the following inclusion criteria (please see “Assessments” section below for an explanation of all abbreviations):Attention Deficit Disorder inattentive type or hyperactive type or combined type according to DSM-IV criteria (ADHS-SB ≥18; WURS-K ≥30; WRI = adult ADHD).No additional serious physical, neurological, or psychiatric disorders with the exception of moderate depression (BDI-II score <28) and personality disorders, however, antisocial (SCID-II) or borderline personality disorders (BSL-23 ≤ 47) were excluded.Full scale IQ >80. 

Participants are excluded based on the following:Self-reported diagnosis of the following current symptoms: Serious physical illness or chronic diseases such as lung disease, heart disease, diabetes, hypertension, and rheumatic diseases; neurological disorders including Parkinson’s disease, stroke, multiple sclerosis and epilepsy; or indicated psychiatric disorders including bipolar disorder, psychosis, obsessive-compulsive disorder, chronic tics, Tourette syndrome, and suicidal behavior.Previous participation in another neurofeedback study.

The initial screening is conducted via phone and questionnaires are mailed to check for the inclusion criteria. The ADHD diagnostic assessment (see Table 1) will be scheduled if inclusion criteria are met. If the participants are on medications such as any short-acting stimulants, they are asked not to take them for at least 24 h prior to each assessment. For the neurofeedback treatment period, they may take their medication but on a stable dose. We do not stratify randomization for medication as we expect the usage to be very diverse.

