### Randomization and blinding

The randomization is conducted in two steps: first a blockwise randomization, and second a pairwise randomization for age, sex and IQ. We determined a grouping order (EEG = 1; NIRS = 2; and EMG = 3). If the participant does not fit into group 1, he/she is matched to group 2 and if not group 2, then group 3. For the next participant, the matching process starts in group 2 and so forth.

The participants are not blinded to the treatment condition, as it is easier to achieve physiological self-control knowing which parameter has to be controlled. Further, blinding was not possible, due to the different feedback methods that made it obvious which treatment was being applied and received (for example, NIRS vs. EEG measurement setup). The different methods are used in different labs and with different technical requirements, and therefore, neither blinding of participants nor blinding of assessors was possible.

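### The three-by-four ANOVA treats baseline as an outcome level, so treatment is tested by a diluted group effect or a 6-df interaction, not by the two-arm comparison the trial was sized for

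*Protocol article*

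**What the plan says.** **Model.** Statistical analysis: "All dependent variables will be tested for effects within and between groups by an analysis of variance (ANOVA) (three groups x four assessment points". The Study flow section places the assessments before treatment, after 15 sessions, after 30 sessions and at 6 months, so the pre-treatment value is one of the four levels. That section then adds "If normal distribution cannot be assumed, non-parametric tests will be used".

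**Primary outcome.** Primary and secondary endpoints names change in core symptoms on ADHS-SB, FEA-AFB and WRI. Table 1 schedules ADHS-SB and FEA-AFB four times, but WRI only at screening, post-test and follow-up.

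**Sample size.** The calculation cites a meta-analysis that "showed a grand mean effect size of 0.81 for improvements in inattention in children with ADHD by EEG neurofeedback training". It continues: "Assuming a pre-defined α of 0.05, a power criterion of at least 80%, and one-sided testing", and "such an effect size would indicate a required sample size of n = 20 per treatment group".

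**Allocation.** Methods/Design describes "feedback groups (n = 20 each) stratified for age, sex, and educational level". Randomization and blinding describes "a pairwise randomization for age, sex and IQ". On medication, the eligibility section says "We do not stratify randomization for medication as we expect the usage to be very diverse".

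**Conclusion sought.** The Discussion rests the case for a new treatment option on one or both feedback types being superior to the control.

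**The concern.** Before treatment the arms can differ only by chance. A group main effect averaged over all four visits therefore includes one visit with a true difference of zero. The test that does use baseline, group by time, asks whether three profiles differ in any way over four visits. It points to no arm, no visit and no direction. The conclusion in the Discussion needs two specific quantities, SCP minus EMG and NIRS minus EMG, and the sample size was set for one such comparison. The stated model does not target either. A significant interaction could come from a difference between the two active arms or from follow-up alone, and a non-significant one could hide a useful contrast.

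At stake are precision in a trial of 20 per arm and a clear answer to the efficacy question.

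**Working it through.** **1. The plan's own figure.** Inputs from Sample-size calculation: d = 0.81, one-sided α = 0.05, power at least 80%. The normal approximation gives 19 per arm. The exact two-sample t-test gives 20 per arm with power 80.8%. The stated 20 reproduces as a one-sided comparison of two arms.

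**2. Degrees of freedom.** Group by time has (3 − 1) × (4 − 1) = 6 df. For WRI, with three assessments, it would have (3 − 1) × (3 − 1) = 4, so the stated layout cannot be fitted to that primary measure.

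**3. Dilution of the group main effect.** Take true differences from EMG of 0, 0.4, 0.81 and 0.81 SD at the four visits. The 0.81 is the plan's figure; the half-way value of 0.4 at mid-treatment and the persistence to follow-up are assumptions.

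- Mean over four visits: (0 + 0.4 + 0.81 + 0.81)/4 = 0.505.
- Mean over the three post-baseline visits: 2.02/3 = 0.673.
- With equal correlation ρ between visits, the variance of a person's four-visit mean is (1 + 3ρ)/4 = 0.475/0.625/0.775 for ρ = 0.3/0.5/0.7.
- Standardised effect: 0.505/√0.475 = 0.73, 0.505/√0.625 = 0.64, 0.505/√0.775 = 0.57.

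So the group main effect weakens as the visits become more correlated.

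**4. Baseline adjustment against change scores.** Variance factors per person at one visit are 2(1 − ρ) for change and 1 − ρ² for ANCOVA. Their ratio is (1 + ρ)/2 = 0.65/0.75/0.85, below 1 for every ρ below 1. For one contrast at post-test under the plan's one-sided 0.05 (normal approximation), ANCOVA has power 85.1/90.5/97.4% and change from baseline 69.8/82.0/95.2%.

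**5. Simulated power.** 20 per arm, both active arms with the effects in step 3, no dropout. F tests at 5%; Bonferroni contrast two-sided. The correlation ρ is not in the documents, so a range is shown. Figures are good to about two points.

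| Test | ρ = 0.3 | ρ = 0.5 | ρ = 0.7 |
|---|---|---|---|
| Group × time, 6 df | 56% | 73% | 93% |
| Group main effect | 65% | 52% | 43% |
| Baseline-adjusted group test at post-test, 2 df | 77% | 85% | 95% |
| One baseline-adjusted contrast, Bonferroni for two | 65% | 73% | 89% |

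The 2-df adjusted test gains 77 − 56 = 21, 85 − 73 = 12 and 95 − 93 = 2 points over the interaction. Under the null all the F tests rejected in about 5% of runs.

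**6. Other effect patterns.** If the full 0.81 SD is present from mid-treatment on, the interaction has 59/76/95%, the group main effect 81/69/59% and the 2-df adjusted test at post-test 77/85/96%. If NIRS has d = 0.40 and ρ = 0.5, the interaction falls to 57–58%, while the SCP-EMG contrast keeps 72–74% after Bonferroni.

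**The case against.** **The interaction already uses baseline.** This stands. The primary outcome is change, group by time compares changes, and the text does not name the group main effect as the efficacy test. The main-effect figures therefore matter only if that test is read as evidence of efficacy.

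**The loss depends on an unknown correlation and on the comparator.** This also stands. At ρ = 0.7 the like-for-like gain is about 2 points. A Bonferroni-corrected contrast equals the interaction at 0.5 (73% each) and falls below it at 0.7 (89% against 93%) when both arms work. With an early, sustained effect at ρ = 0.3, the group main effect (81%) even beats the adjusted test at post-test (77%).

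**Covariates and contrasts may be in an analysis plan that is not shown.** This is fair for the covariate list. The electromyogram feedback section itself says that expectancy will enter the analysis, so the ANOVA sentence is not the whole model. But the treatment of baseline as a level is stated, not omitted.

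**Stronger readings that the documents do not support.** A reader might infer:

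- That the ANOVA loses balance. Balance comes from allocation; a model can only correct for chance imbalance.
- That people who miss a visit are dropped. The text does not say so.
- That the non-parametric fallback changes the hypothesis. No test is named, and rank methods for group by time exist.
- That unstratified medication distorts the result. Neither the share of users nor its prognostic strength is given. The eligibility section asks for a stable dose during treatment and for short-acting stimulants to be withheld for at least 24 h before assessments.
- That regression to the mean creates efficacy. All arms face the same ADHS-SB entry threshold, and the Discussion rests efficacy on superiority over EMG. The caution applies only to within-arm change.

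**Conclusion.** The point holds as one of efficiency and targeting, not of bias. The fixed model makes baseline an outcome level, spreads the treatment question over 6 df without direction, does not match the one-sided two-arm test behind the sample size, and cannot be fitted as written to WRI. Against a 2-df baseline-adjusted test at post-test, the interaction gives up about 21, 12 and 2 points of power at correlations of 0.3, 0.5 and 0.7. These figures assume equal correlation between visits, no dropout and the effect pattern in step 3. A reader might infer that the planned test is invalid or always clearly weaker; neither follows. What remains at any correlation is that the active-versus-EMG differences, which the Discussion needs, are not what the stated model estimates.

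**What to change.** For the primary symptom scales, replace the three-by-four ANOVA by a mixed model (or ANCOVA) on the available post-baseline visits, with baseline score, arm, visit and arm × visit. For WRI these visits are post-test and follow-up. Name SCP-EMG and NIRS-EMG at post-test as the efficacy estimates, and state the sidedness and any correction for two contrasts. Report within-arm change descriptively.

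Add the allocation factors once the two descriptions are reconciled: Methods/Design gives age, sex and educational level, while Randomization and blinding gives age, sex and IQ. A simple yes/no medication term is optional, as a sensitivity analysis.

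The cost is a change of analysis wording and a few degrees of freedom. All the variables are already collected.
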